**Other factors**

- Heart disease (heart or blood vessel condition; yes, no, I don’t know);
- Low to moderate alcohol consumption (standard units consumed per day);
- Smoking habits (i.e. current smoker; yes or no);
- Chronic kidney disease (yes, no, I don’t know)
- Cholesterol (High cholesterol; yes, no, I don’t know)

**Impact Evaluation**

The evaluation will be based on these overarching questions from the Australian Government impact evaluation framework [27]:

- Did the initiative make a difference?
- How much of a difference did the initiative make?
- For whom, in what situations, and in what ways did the initiative make a difference?
- To what extent can a specific impact be attributed to the initiative?
- How did the initiative make a difference?
- Will the initiative work elsewhere?
- What is needed for the initiative to work elsewhere?

**Study 2**

A semi-structured questioning route beginning with general opening questions and several key questions and sub questions. The questioning route will be organised into themes; (1) Brain Bootcamp overall; (2) Effectiveness of intervention strategies (a) brain health risk profile (b) Brain Bootcamp box items (3) Recommendations and Improvements. Questions have been developed based on feasibility and acceptance interviews employed in previous public health interventions[40-42].

**Study 3**

Participants will be divided into two groups (Group A and Group B) and administered the Virtual Reality Cognitive Screener (TICS-M) and the Telephone Interview for Cognitive Status-Modified within one week.

A flow chart of Study 3 is provided below:

[figure not shown]

**Memory Performance:**

Traditional: Classification of cognitive status will be conducted by administering a 23 question Telephone Interview for Cognitive Status-Modified (TICS-M) either in person on over the phone. This will include scoring on name, date, age, phone number, ability to count backwards from 20 to 1, immediate recall of 10 words, counting backwards from 100 by 7, the naming of objects and concepts, repetition of phrases, the name of current political figures, tapping 5 times, naming opposites of common words, and delayed recall of 10 words. The maximum score is 50 points. The TICS-M will classify individuals as having no or minimal cognitive impairment (>40) or possible mild cognitive impairment (≤ 20) or moderate cognitive impairment (≤12). The TICS-M has been previously validated [43] with strong psychometric properties[44]. Prior studies have shown that the TICS-M has a high sensitivity in the detection of dementia[45, 46] but a low positive predictive value [43].

A further 5 minutes will be used to calculate the scores and to disseminate this finding to the participant at the end of the session. Whilst researchers are happy to discuss the findings further if the client wishes, if any participant has been identified as having a low memory score <27 they will be referred to their local GP to obtain a more comprehensive assessment.

Virtual Reality Cognitive Screener (VRCS): Developed using the Unity game engine, the application places the user on a virtual in a virtual restaurant modelled to be similar to an Australian café. The user’s role will be that of the waiter, needing to serve restaurant customers. The VRCS will be developed using Unity’s WebGL build option. This will allow the VRCS to run in current versions of most major web-browsers. Suggested browsers are (in no particular order) Microsoft Edge, Mozilla Firefox and Google Chrome. (Videos of the VRCS in development are uploaded in “Other Project Material”)

Using the VRCS, participants will gain a score out of 165. The score will be achieved by the participant serving up to five tables of customers correctly – at the most basic level this consists of one table of two customers and at the highest level this will be four tables of four customers. Participants are asked to remember the items ordered by customers from a particular table and to correctly collect the food items from the kitchen and bring it back to the right customer. The complexity of a customer orders will increase with each table.

The VRCS is designed to assess four cognition domains which is briefly described below:

1. Free recall: To correctly input the customer’s order onto a virtual whiteboard immediately after taking the order
2. Delayed recall: To correctly re-input the customer’s order onto the virtual whiteboard after a typical distractor task (e.g., customer rings to book a table)
3. Cued recall: To correctly identify the customer’s order on the kitchen counter amongst other food orders
4. Spatial recall: To bring the customer order back to the right table to the right customer.

As this is still in the development and is not a validated measure to reliably predict memory scores, participants will not be informed of their score. They will only be provided with the number of orders they got correct at the end of the game.

**Feedback survey:** Participants will also be invited to participate in an online feedback survey once the Virtual Reality Cognitive Screener is completed. The survey will be about the acceptability and feasibility of the Virtual Reality Cognitive Screener. Questions have been developed based on previous evaluation of virtual reality screeners used in health and medical settings with older adults [42]. There are six questions, and the answers will be rated on a 5-point Likert scale (1 - strongly disagree, 2 - disagree, 3 - neutral, 4 - agree, 5 - strongly agree). Total feedback scores will be calculated by summing the scores from the six questions.

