**Study 3**

### STUDY 3 PRIMARY OBJECTIVES

1. To determine the validity and reliability of new virtual reality cognitive screener in assessing cognitive function in older adults
2. To assess the ability of the virtual reality cognitive screener to discriminate between cognitively intact and cognitively impaired participants.

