**Study 3**

Descriptive data will be compared between the groups using a two-sample t test and the Fisher exact test for continuous and categorical variables, respectively. Summary statistics will be calculated individually for the Virtual Reality Cognitive Screener, traditional cognitive assessment and questionnaire-dependent feedback scores. Younger and older adults (and older adults with cognitive impairment) cognitive performance on all measures will be compared using the two-sample t tests.

Performance scores will be analysed at each task level, given a total score, and compared between the older cognitive-intact and younger groups using the methods described above, as appropriate. Correlation between performance scores and other variables will assessed using Pearson correlation. A logistic regression will performed based on the total performance scores, followed by ROC analysis to assess its predictive capability to discriminate between cognitively intact and cognitively impaired individuals. Analyses will be performed using SPSS V22.0.

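### Study 3's TICS-M classes leave scores 21 to 40 without a class, so the intact/impaired status that the ROC analysis needs is not defined for anyone scoring there

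*Protocol*

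**What the plan says.** Protocol Section 7, Study 3, Memory Performance, makes the telephone instrument the classifier: "Classification of cognitive status will be conducted by administering a 23 question Telephone Interview for Cognitive Status-Modified (TICS-M"). It adds: "The maximum score is 50 points". The classes are "no or minimal cognitive impairment (>40) or possible mild cognitive impairment (≤ 20) or moderate cognitive impairment (≤12"). The next paragraph sets a separate line for feedback to participants: anyone with a "low memory score <27 they will be referred to their local GP".

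Section 8.2, Study 3, uses cognitive status in three places. A logistic regression on the total performance score is "followed by ROC analysis to assess its predictive capability to discriminate between cognitively intact and cognitively impaired individuals". Performance scores are "compared between the older cognitive-intact and younger groups". The t-tests between age groups also name older adults with cognitive impairment.

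The second Study 3 primary objective in Section 3 is to assess whether the screener can "discriminate between cognitively intact and cognitively impaired participants". Hypothesis 4 in Section 2 says the same.

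**The concern.** A logistic regression and an ROC curve need a binary outcome for every person analysed. The only rule the protocol gives for that outcome does not cover its own scale, and Section 8.2 supplies no boundary to replace it. A participant scoring, say, 30 is neither intact nor impaired by the text.

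The analyst then has two options. One is to apply the rule literally, drop everyone in the middle and compare the two ends of the scale. That is an easier discrimination task than a screener faces in use. The other is to choose a boundary during analysis, possibly with the data in view. Either way, the AUC for a primary objective does not rest on a rule fixed in advance.

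**Working it through.** **1. Coverage of the scale.** Inputs from Section 7: maximum 50; classes >40, ≤20 and ≤12; referral line <27. The minimum is not stated, so I assume 0, which gives 51 integer scores.

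| Score | Number of scores | Class in Section 7 | Below the <27 line? |
| --- | --- | --- | --- |
| 0–12 | 13 | moderate (also within ≤20) | yes |
| 13–20 | 8 | possible mild | yes |
| 21–26 | 6 | none | yes |
| 27–40 | 14 | none | no |
| 41–50 | 10 | no or minimal | no |

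Unclassified: 6 + 14 = 20, and 20/51 = 39% of possible scores. Six of those 20 are called low for referral.

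**2. Is the status defined elsewhere?** Section 8.2 uses intact and impaired without a cut-off. Sections 2 and 3 use the terms without defining them. Section 5.1 excludes diagnosed dementia but gives no score. Nothing fills the gap.

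**3. How many people might fall in the gap?** The protocol gives no TICS-M mean or SD, so this part is assumption only. Take a normal distribution truncated to 0–50 with half-unit bounds:

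share = [F(40.5) − F(20.5)] / [F(50.5) − F(−0.5)]

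| Assumed mean | Share in 21–40, over SD 3, 5, 7 | Share at ≤20, over SD 3, 5, 7 |
| --- | --- | --- |
| 25 | 73–93% | 7–26% |
| 30 | 85–100% | 0.1–9% |
| 35 | 78–97% | 0–2% |
| 38 | 66–80% | 0–0.6% |
| 40 | 55–57% | 0–0.3% |
| 42 | 31–47% | at most 0.1% |
| 45 | 7–33% | under 0.1% |

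The gap holds a majority for assumed means from 25 to 40, but not at 42 or above. At those higher means almost nobody is classed as impaired.

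**4. Direction of the effect if only the extremes are kept.** This is an illustration. Assume a TICS-M mean of 30, SD 5, and a correlation r = 0.30 between screener and TICS-M (the effect size in Section 8.1, borrowed as an assumption). With m the mean and v the variance of the standardised TICS-M within a group:

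AUC ≈ Φ( r(m₁ − m₂) / √[2(1 − r²) + r²(v₁ + v₂)] )

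- Above 40 against 20 or below: the standardised limits are (40.5 − 30)/5 = 2.1 and (20.5 − 30)/5 = −1.9. Group means are 2.462 and −2.285, with variances 0.109 and 0.120. The numerator is 0.30 × 4.747 = 1.424 and the denominator √(1.82 + 0.09 × 0.229) = 1.357. The AUC is Φ(1.05) ≈ 0.85.
- Everyone kept, split at the document's <27 line (used only because it is a number on the page, not as a proposal): the limit is (26.5 − 30)/5 = −0.7. Group means are 0.412 and −1.290, with variances 0.542 and 0.238. The numerator is 0.30 × 1.702 = 0.511 and the denominator √(1.82 + 0.09 × 0.780) = 1.375. The AUC is Φ(0.371) ≈ 0.64.

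The same weak association gives about 0.85 when the middle is dropped and about 0.64 when it is kept.

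**The case against.** The best defence is that details of analysis belong in a statistical analysis plan, which is not at hand. That does not answer the point. The protocol did not leave the rule open; it fixed one that fails on its own scale. A later plan would either repeat the gap or depart from the protocol.

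Other parts of the defence do stand, and they limit what can be claimed. Some stronger readings that a reader might infer are not supported:

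- **That most participants are unclassified.** This depends on an assumed distribution. Half of Study 3 is adults aged 18 and over, who may score higher than the older group.
- **That the young adults will be pooled into the ROC as intact.** Section 8.2 does not say so. It distinguishes younger, older intact and older impaired adults. The Brain Bootcamp part of Section 1 and Section 4.1 place discrimination in older adults. The ROC sentence merely names no age group.
- **That the AUC is bound to be biased upward.** Dropping the middle tends to do that. A boundary chosen later does so only if it is picked to favour the screener, and an error-prone reference test can pull the AUC towards 0.5. The protocol also does not say that unclassified people will be dropped.
- **That ≤12 lying within ≤20 is a contradiction.** It reads naturally as a more severe grade within a wider one.
- **That the referral line must equal a class boundary.** A referral rule can serve a different purpose. What remains is that 21 to 26 is labelled low and has no class.

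Study 3 is also a feasibility study. Its acceptability results and its planned Pearson correlations do not need the classification.

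**Conclusion.** The point holds in a limited form. As written, the classification assigns no status to anyone scoring 21 to 40, which is 20 of 51 integer scores if the minimum is 0. No other text supplies the intact/impaired outcome for the logistic and ROC analysis, or for the comparisons involving older intact or older impaired adults. Because that analysis is the one that answers a primary objective, the gap should be closed before data are seen.

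The coverage gap rests on the protocol's own figures plus the assumed minimum. The number of people affected cannot be stated from the protocol. The AUC comparison shows direction under stated assumptions and does not predict the trial's result.

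**What to change.** Before any Study 3 data are seen:

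1. In Section 7, state one intact/impaired boundary that assigns every possible TICS-M score to exactly one class. Grades within the impaired class can stay. The sponsor decides the values.
2. In Section 8.2, refer to that boundary as the outcome of the logistic and ROC analysis and as the definition of the older intact and older impaired groups.
3. Reconcile the <27 referral line with the classes, or state that it serves another purpose and why it differs.
4. In Section 8.2, state that the ROC analysis is run in the older adults (65+), in line with Sections 1 and 4.1.

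The cost is protocol wording; no extra data or participants are needed. The reported AUC may be lower than one computed from the extremes alone.

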**Analysis plan**

Study 1 Descriptive analysis of baseline profile of participant demographics (age, gender, economic status) will be presented.

Non-parametric correlations and paired sample t-tests will be conducted to examine and analyse changes in primary outcome (dementia awareness, brain health risk profile) at baseline to three months.

**Study 2** Interview data will be analysed qualitatively for content and themes that emerge, and coded and categorised using N Vivo software

**Study 3** Descriptive statistics will be calculated for participant demographics and domains of the virtual reality screener and the traditional cognitive assessments. This will include percentage of participants who successfully completed the virtual reality cognitive assessments, time taken to complete the virtual reality cognitive assessment module, and scores from the feedback questionnaire.

Correlational analyses and receiver operating curve (ROC) will be conducted for performance scores on the virtual reality assessment module and scores on other cognitive assessment tests.

Duration of the Study 24 months

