# 2. HYPOTHESIS

Our hypotheses are that:

1. The Brain Bootcamp campaign will improve older adults’ brain health risk profile at follow-up assessment.
2. The Brain Bootcamp campaign will increase older adults’ dementia awareness and knowledge of modifiable risk factors.
3. The virtual reality cognitive screener is feasible and acceptable for use with younger and older adults.
4. The virtual reality cognitive screener is able to discriminate between cognitively intact and cognitively impaired participants.

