**Study 3**

General public participants who meet the inclusion criteria and are over the age of 18 will be recruited to participate in both a virtual reality cognitive screener and a traditional telephone based cognitive screening test. For the older adults, a sub-set of older adult participants from Study 1 will be contacted via email to see if they are interested in participating. This will be based on their scores in the brain health risk profile, identified using the LIBRA index, which is shown to be a valid predictor of the development of dementia [19-21]. Younger adults will be recruited from the general public via social media and other relevant channels. All participants will be provided with an opportunity to participate in a feedback survey after they have completed the virtual reality screener. Questions will be about the acceptance, perception and experience of virtual reality.

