**Study 3**

The participant will be enrolled into the study after the informed consent process has been completed. We request general public participants to include identifiable information to ensure they can be contacted to participate in both the traditional cognitive assessment and virtual reality cognitive screener within the same week. Upon completion of the first screening assessment general public participants will receive a study enrolment number which will be pre-populated on the second screening assessment to enable the research team to link their results. Study 1 participants who wish to participate in study 3 will continue to use their study 1 enrolment number. After completing the virtual reality screener participants will be invited to participate in a short online feedback survey.

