**Study 3**

Study 3 will include community-dwelling participants aged 18 years and over. Study 3 participants are consenting to participate in a (1) using identifiable information provided in study 1 to be contacted for study 2; (2) participate in a virtual reality cognitive screener or; (3) participate in a traditional cognitive assessment via telephone (4) participate in a feedback survey about the acceptability and feasibility of the Virtual Reality Cognitive Screener .

Participants from Study 1 will be given the opportunity to participate in Study 3 based on their brain health profile at baseline. Adults from the general public participants not involved in the Brain Boot Camp campaign will also be recruited to participate in the study. For the virtual reality cognitive screener, participants will provide online consent and receive a link to participate in the virtual reality screener online. For the traditional cognitive assessment via telephone, researchers will also seek verbal consent at time of administration before undertaking the assessment to ensure participants understand the study. After completion of the virtual reality screener participants will be invited to participate in a brief online feedback survey.

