**Study 3**

Participants will be recruited from the general public who are over 18. Study 1 participants will be contacted to give them an opportunity to participate in Study 3, based on their brain health risk scores. Information about their memory performance will be collected as outlined in **Section 7.** Both the Virtual Reality Cognitive Screener and telephone based cognitive assessment will take approximately 30 minutes to complete. A random selection of half of each of the younger and older adults participants will receive the traditional telephone cognitive assessment (Group A), whilst the other half will complete the Virtual Reality Cognitive Screener (Group B). Then, the groups will swap and Group A will complete the Virtual Reality Cognitive Screener , whilst Group B completes the telephone cognitive assessment. Both assessments will then be complete within a week of each other. After completion of the virtual reality cognitive screener, participants will be invited to provide feedback via a voluntary online survey about the feasibility and acceptability of their virtual reality experience.

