**Table 2. Assessment measures for participants**

| Study 1 | | |
| --- | --- | --- |
| Outcome | Data collection instrument | |
| Primary Outcomes | | |
| Dementia Awareness | Dementia Awareness Questionnaire [22, 23] | |
| Brain health risk profile | LIBRA index [19] | |
| Motivation | Motivation to Change Lifestyle and Health Behaviour for Dementia Risk Reduction (MCLHB-DRR)[24] | |
| Quality of life | EuroQol Group EQ-5D-5L [25] | |
| Social networks | Lubben Social Network Scale (LSNS-6) [26] | |
| Overall experience | Impact Evaluation survey [27] | |
|  |  |  |
| Study 2 | | |
| Outcomes | | |
| Behaviour change/ impact of campaign | Semi-structured interviews | |
| Study 3 | | |
| Outcomes | | |
| Memory performance | Virtual reality assessment (developed in house by our researchers)  Telephone Interview for Cognitive Status-Modified (TICS-M) | |
| Acceptability | Research-team generated feedback survey | |

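### The VR acceptability survey is offered only after the screener is completed, so its ratings describe completers and probably lean favourable

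*Protocol*

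**What the plan says.** Five places in the protocol describe when the feedback survey is offered, and all put it after completion of the VR screener:

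- Section 6.2, Study 3: "All participants will be provided with an opportunity to participate in a feedback survey after they have completed the virtual reality screener".
- Section 6.4, Study 3: "After completing the virtual reality screener participants will be invited to participate in a short online feedback survey".
- Section 6.5, Study 3: "After completion of the virtual reality screener participants will be invited to participate in a brief online feedback survey".
- Section 6.6, Study 3: "After completion of the virtual reality cognitive screener, participants will be invited to provide feedback via a voluntary online survey". This is the place that also calls the survey voluntary.
- Section 7, Study 3, feedback survey: "Participants will also be invited to participate in an online feedback survey once the Virtual Reality Cognitive Screener is completed".

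Table 2 names one instrument for acceptability: "Research-team generated feedback survey". Section 7 gives it six items, each scored 1 to 5 and summed.

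Hypothesis 3 in Section 2 reads: "The virtual reality cognitive screener is feasible and acceptable for use with younger and older adults". Acceptability is also named in the first Study 3 objective of the Summary and in the design statement of Section 4.1. The Summary's analysis plan for Study 3 lists, together with completion time and feedback scores, the "percentage of participants who successfully completed the virtual reality cognitive assessments".

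**The concern.** The survey rule selects on something closely tied to what the survey measures. A person who opens the screener and gives up because it is confusing, tiring or technically awkward is an informative witness on acceptability, and under the written rule is not asked.

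The protocol itself foresees non-completion, since it plans to report a completion percentage. It is also plausible on the design described. The screener reaches participants as an online link (Section 6.5), takes about 30 minutes (Section 6.6), runs in a web browser and becomes harder from table to table (Section 7).

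At stake is the acceptability half of hypothesis 3. Section 1 says the screener work will inform wider delivery of gamified cognitive tests, where people who stop part-way count. Because this is a data-collection rule, no later analysis can recover ratings that were never requested.

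**Working it through.** **Is there any other route?** The five descriptions agree that the invitation follows completion. The wording in Section 6.2 begins with all participants, but it too places the offer after they have completed. Table 2 lists no second acceptability instrument. Study 2, by contrast, deliberately samples people who dropped out of Study 1 (Sections 6.2, 6.5 and 8.1). Nothing comparable is written for people who stop the VR screener.

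**Who exactly is missed?** The score in Section 7 depends on serving tables correctly, and participants see their number of correct orders when the game ends. Someone who reaches the end with a poor score is therefore invited. Only those who do not reach the end are left out.

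**Is there a figure to reproduce?** No. The protocol states no expected completion rate, feedback mean or acceptability threshold. What follows is an illustration.

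Inputs:
- Scale: six items at 1 to 5, so the total runs from 6 × 1 = 6 to 6 × 5 = 30 (Section 7).
- q, the proportion of starters who do not complete: not given; assumed 5% to 30%.
- C, the completer mean: not given; assumed 24.
- U, the mean that non-completers would have given: not given; assumed 12 to 18, with 24 and 26 as checks on direction.

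The mean over all starters is (1 − q) × C + q × U. The completers-only mean is C. The excess is

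C − [(1 − q) × C + q × U] = q × (C − U).

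For example, q = 0.20 and U = 12 give 0.20 × (24 − 12) = 2.4 points.

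| q | U = 12 | U = 18 | U = 24 | U = 26 |
| --- | --- | --- | --- | --- |
| 5% | 0.6 | 0.3 | 0 | −0.1 |
| 10% | 1.2 | 0.6 | 0 | −0.2 |
| 20% | 2.4 | 1.2 | 0 | −0.4 |
| 30% | 3.6 | 1.8 | 0 | −0.6 |

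**The same question as a proportion.** Suppose 80% of completers find the screener acceptable (assumed). With non-completers' views unknown, the proportion among all starters lies between 0.8 × (1 − q), if none of them would accept it, and 0.8 × (1 − q) + q, if all would:

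- q = 5%: 76% to 81%
- q = 10%: 72% to 82%
- q = 20%: 64% to 84%
- q = 30%: 56% to 86%

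Both illustrations treat every completer as answering. The survey is voluntary, so non-response among completers adds further uncertainty that they do not show.

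**The case against.** The strongest reply is that completion is reported alongside the feedback scores, so a reader will see how many people did not finish and can weigh the ratings accordingly. Study 3 is a feasibility study, and no cut-off or decision rule hangs on the feedback score. This stands as mitigation: the loss is visible under feasibility. It does not supply the missing ratings or the reasons for stopping.

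Four stronger readings are tempting, and the protocol does not support them.

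- A reader might infer that people who do badly never rate the screener, or that negative views cannot be recorded. Low scorers who reach the end are invited, and any respondent may choose the lowest category on every item.
- A reader might infer that overstatement is established. Direction and size depend on quantities the protocol does not give. Upward is the plausible direction, but the excess is zero if ratings do not differ and slightly negative if non-completers would rate higher.
- A reader might infer that a planned young–old test of feedback scores is distorted. Section 8.2 plans summary statistics for feedback, and its explicit young–old t tests concern cognitive performance. Its general sentence on comparing descriptive data between groups might cover feedback, but that is an interpretation.
- A reader might see the eligibility requirements in Section 5.1 (internet access, vision, ability to use a mouse) as the same fault. They openly define the population for a browser-based, mouse-operated test and are not a defect of the survey rule.

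The word completed might also have been meant to cover any session that has ended. If so, one clarifying sentence would settle the point. As written, the five descriptions do not say so.

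**Conclusion.** The point holds in a limited form. The only acceptability instrument in Study 3 is offered after completion, with no route for people who start and stop early. Its ratings therefore describe completers, while hypothesis 3 concerns younger and older adults in general, and they probably lean favourable.

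That the rule is written this way is certain. The size of its effect is unknown: about 0.3 to 3.6 points on the 6 to 30 scale under the assumptions of 5% to 30% non-completion, a completer mean of 24 and a non-completer mean of 12 to 18, and nothing if the two groups would rate alike. The change is worth making because it is cheap and has to be in place before the data are collected.

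**What to change.** 1. Offer the survey to everyone who opens the VR screener, triggered at exit or time-out as well as at completion.
2. Send an automated email with the survey link to those who started but did not finish. Section 6.4 already provides for identifiable details so that participants can be contacted, and the Section 6.5 consent list already includes the feedback survey.
3. Add a question on the reason for stopping.
4. Report ratings for all starters, with completers as a subset, beside the completion rate and the survey response rate.
5. Count people who consented but never opened the screener, or could not load it, under feasibility. They have no experience of the screener to rate.
6. Use the same wording in Sections 6.2, 6.4, 6.5, 6.6 and 7.

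The cost is a changed survey trigger, one automated email, one added question and a protocol amendment reported to the ethics committee under Section 9.3. No extra participants or visits are needed. The downside is that the acceptability figure may fall and some ratings will come from people who used only part of the screener, which is why completers should also be shown separately.
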